## Abstract

Malaria remains a major public health burden despite approval for implementation of a partially effective pre-erythrocytic malaria vaccine. There is an urgent need to accelerate development of a more effective multi-stage vaccine. Adults in malaria endemic areas may have substantial immunity provided by responses to the blood stages of malaria parasites, but field trials conducted on several blood-stage vaccines have not shown high levels of efficacy.  We will use the controlled human malaria infection (CHMI) models with malaria-exposed volunteers to identify correlations between immune responses and parasite growth rates
*in vivo*.  Immune responses more strongly associated with control of parasite growth should be prioritized to accelerate malaria vaccine development. We aim to recruit up to 200 healthy adult volunteers from areas of differing malaria transmission in Kenya, and after confirming their health status through clinical examination and routine haematology and biochemistry, we will comprehensively characterize immunity to malaria using >100 blood-stage antigens. We will administer 3,200 aseptic, purified, cryopreserved
*Plasmodium falciparum* sporozoites (PfSPZ Challenge) by direct venous inoculation. Serial quantitative polymerase chain reaction to measure parasite growth rate
*in vivo* will be undertaken. Clinical and laboratory monitoring will be undertaken to ensure volunteer safety. In addition, we will also explore the perceptions and experiences of volunteers and other stakeholders in participating in a malaria volunteer infection study. Serum, plasma, peripheral blood mononuclear cells and whole blood will be stored to allow a comprehensive assessment of adaptive and innate host immunity. We will use CHMI in semi-immune adult volunteers to relate parasite growth outcomes with antibody responses and other markers of host immunity.

**Registration:** ClinicalTrials.gov identifier
NCT02739763.

## Abbreviations

ACT: artemisinin combination therapy; ADRB: Antibody dependent respiratory burst assay; CHMI: controlled human malaria infection; CHMI-SIKA: controlled human malaria infection in semi-immune Kenyan adults; DVI: Direct venous inoculation; GIA: Growth Inhibition Assay; OPA: Opsonic Phagocytosis Assay; PfSPZ Challenge: Aseptic, purified, cryopreserved
*P. falciparum* sporozoites; qPCR: quantitative Polymerase Chain Reaction; SPZ: Sporozoites.

## Introduction

Malaria remains a disease of global health importance, despite the gains made against reducing morbidity and mortality. The latest estimates of the burden of malaria indicate that 3.3 billion people are exposed with 216 million cases and over 445,000 deaths being reported, with Africa accounting for ~91% of deaths due to malaria
^1^. There has been encouraging progress made in some areas of Africa, but progress has now stalled
^2^. Elimination does not appear realistic in many areas with higher transmission
^3^, and progress is threatened by insecticide and drug resistance
^4,
5^. An effective vaccine strategy is required to deliver sustainable and cost-effective control
^6^. Sub-unit vaccine development to date has focused on a limited pool of empirically selected candidate antigens, and field trials have not shown high levels of efficacy
^7^.

## Malaria vaccine development

The current lead malaria vaccine, RTS,S, a sub-unit vaccine, is based on a single pre-erythrocytic stage antigen the circumsporozoite protein (CSP). It delivers ~30% protection with waning efficacy over a few years
^8,
9^. Whole
*Plasmodium falcipaurm* (Pf) sporozoite (SPZ) vaccines have shown >90% protection against controlled human malaria infection (CHMI) and ~50% protection in the field
^10,
11^. Higher vaccine efficacy would be optimal. One approach would be addition of partner antigens from the blood or transmission stages of the parasite. There are currently few subunit candidate blood-stage vaccines in clinical development: candidate vaccines in clinical efficacy trials are based on only five different antigens, and none have shown high level efficacy against their primary endpoint
^12–
14^.

A critical step in the development of a subunit blood-stage vaccine is identifying which parasite antigens to prioritise as targets for vaccine development.

### Naturally acquired immunity to malaria to inform vaccine selection

One approach to understanding human immunity to malaria to date has been to identify correlates of immunity using cross-sectional surveys of children living in malaria endemic regions, identifying subsequent malaria episodes, and then linking potential correlates of host immunity to outcome
^15–
18^. However, the limitations of this approach include: (a) variation of exposure in the endemic population means some individuals are unexposed to infectious bites, but assessed as if they were “protected”
^19^; (b) parasite exposures are genetically heterogeneous
^20^; (c) heterogeneity of exposure even within a single endemic setting leads to confounding effects (i.e. higher exposure is causally linked to the covariate of interest, to other effector mechanisms of immunity, and also to risk of malaria episodes)
^21,
22^; and (d) the antibody responses of greatest interest may well be those that are infrequently raised by natural exposure and are therefore not well represented in a community cohort
^23^.

 By measuring the parasite growth rates among semi-immune adult volunteers from malaria-endemic regions taking part in controlled human malaria infection (CHMI) studies, we have the opportunity for a complementary measure of human immunity where higher levels of antibody than those generated in children can be studied, and where exposure is controlled thus avoiding the confounding factors described above.

### CHMI studies in semi-immune individuals

CHMI studies in developed countries have until recently depended on exposure to mosquito bites, which place logistic demands in terms of the incubation of blood-stage cultures, feeding and infection of laboratory reared mosquitoes in sufficient numbers, which then cannot be stored. Work in malaria endemic countries can be facilitated by using cryopreserved sporozoites. [name] and colleagues at Sanaria have addressed various technical challenges in developing this technology, including the need to prepare large numbers of aseptic, purified and viable Pf sporozoites ((SPZ) (Sanaria(R) PfSPZ Challenge)) which can be cryopreserved and injected by syringe when required
^24–
31^.

A number of studies have been conducted to date to establish the safety and efficiency of this approach
^24,
25^ and following a scale-up in production, CHMI studies are now possible at a very much greater scale (
Table 1). The direct venous inoculation (DVI) of sporozoites (PfSPZ Challenge) is the most efficient route of administration and provides a reproducible inoculum
^28,
29^. Recent studies have shown that the infection rate produced by intramuscular injection of 75,000 sporozoites (PfSPZ of PfSPZ Challenge) is comparable with 3,200 PfSPZ sporozoites administered by DVI and 5 mosquito infected bites in malaria-naïve volunteers. Thus there are fewer PfSPZ sporozoites required using the DVI route of administration to achieve the same infection rates observed by the intramuscular route of administration
^28^. The DVI route has further been proven to be safe and reliable resulting in infection of all volunteers administered
^29^.

**Table 1. T1:** List of PfSPZ Challenge CHMI Studies in African Endemic Populations
*.

Location	Study Type	Number of Volunteers	Route of Administration	Age (years)	Gender	Malaria Outcome ^1^	Reference
Equatorial Guinea	Vaccine efficacy Vaccine efficacy	52 104	DVI DVI	18–35 18–45	Both Both	TBS ^2^ TBS ^2^	NCT02859350 NCT03590340
Gabon	Infectivity Vaccine efficacy	20 12	DVI DVI	18–30 18–40	Both Both	TBS ^2^ TBS ^2^	34 PACTR201503001038304
Gambia	Infectivity	19	DVI	18–35	Males	qPCR	35
Kenya	Infectivity ^3^	28	IM	18–45	Both	TBS ^2^	31
Mali	Vaccine efficacy ^4^ Vaccine efficacy	62 45	DVI DVI	18–45 18–50	Both Both	TBS ^2^ TBS ^2^	NCT02996695 NCT02627456
Tanzania	Infectivity ^3^ Vaccine efficacy Vaccine efficacy Vaccine efficacy	24 64 24 18 ^^^	ID DVI DVI DVI	20–35 18–35 18–45 18–45	Males Males Both Both	TBS ^5^ TBS ^2^ TBS ^2^ TBS ^2^	30 36 NCT02613520 NCT03420053

*Current status as of 30th October 2019.
^1^Primary measure for malaria treatment/diagnosis;
^2^Studies included qPCR data for secondary parasitaemia analysis;
^3^Studies included dose optimisation for PfSPZ Challenge administration;
^4^PfSPZ Challenge in the context of chemoprophylaxis using chloroquine (PfSPZ-CVac);
^5^Studies included qRT-PCR data for secondary parasitaemia analysis; and ^PfSPZ Challenge including HIV positive individuals (N=9). DVI, direct venous inoculation; IM, intramuscular; ID, intradermal; qPCR, quantitative PCR; and TBS, thick blood smear.

Overall, CHMI studies have been reported to be safe with only myocardial events having occurred in two naïve volunteers (from a total of over 2,000 volunteers who have undergone CHMI), one with prior cardiovascular risk factors and evidence of atherosclerotic infarction, and one without risk factors and a less clear clinical picture
^32,
33^. Furthermore, no participant in CHMI has thus far developed an illness meeting criteria for severe malaria. Thus overall, administration of PfSPZ in CHMI appears to be safe. To date, there are 12 CHMI studies that have been conducted or planned in Africa involving over 450 volunteers with varying degrees of malaria exposure across 6 countries (
Table 1).

## Ethical considerations for CHMI studies in endemic populations

CHMI studies raise ethical issues regarding volunteer safety and as such require that careful medical supervision and mitigation of the risks of challenge. CHMI studies in endemic populations are often carried out in in-patient settings requiring the volunteers to stay at study premises for a considerable amount of time to ensure safety and to prevent acquiring natural malaria infections
^34,
36^. There has been extensive consideration of the appropriate financial compensation
^36^. Although volunteers would be motivated to participate for altruistic reasons, care should be observed to ensure that the levels of payments offered are not an undue influence which would cause the volunteers’ judgement to be unduly influenced and therefore minimise the risks and discomforts involved
^36^. However, CHMI studies may require that volunteers are isolated from others, leading volunteers to incur substantial expenses and inconvenience, and these expenses must be compensated for to ensure that volunteers are not financially worse off as a result of participating. The informed consent process requires that the participant understands that they can withdraw from the study at any point with no penalty or interference
^36,
37^. Nesting ethical and social empirical work within the CHMI study, we have recently shown the importance of examining participant perceptions in volunteering in CHMI studies
^38^ and aim to further explore experiences with a larger sample set and other stakeholders. 

## Study protocol

This study protocol has been written in accordance with the SPIRIT guidelines for reporting clinical trials. A completed SPIRIT checklist is available at the Harvard Dataverse
^39^.

### Study aim and objectives

CHMI-SIKA study will investigate how the
*in vivo* parasite growth rate of
*Plasmodium falciparum* (Pf) is modified by pre-existing immunity measured by antibody levels to blood-stage antigens.

### Primary objective

The primary objective is to measure the correlations between antibody levels to defined and well characterised malaria antigens and growth rates of
*P. falciparum* in volunteers undergoing CHMI.

### Secondary objectives

The secondary objectives of the CHMI-SIKA study are:

To confirm the safety of CHMI administered by DVI in semi-immune volunteers.To measure parasite growth rates in semi-immune volunteers.To establish a sample set for the study of immunity to malaria and its effect on parasite growth following CHMI in semi-immune volunteers.To explore the understanding, motivations for participation, and experiences of volunteers and other stakeholders.

### Study design

CHMI-SIKA is an open label, non-randomised trial involving 200 healthy volunteers aged from 18 to 45 years recruited over a period of 5 years with varying degrees of immunity from malaria endemic areas in Kenya. CHMI will comprise the direct venous inoculation of aseptic, purified, cryopreserved PfSPZ (Sanaria(R) PfSPZ Challenge). Volunteers will be enrolled for PfSPZ Challenge in groups of 20–60 volunteers per CHMI event (henceforth referred to as CHMI cohorts) at any given time. We will screen all volunteers for varying degrees of immunity, ensuring a range of volunteers with low and high antibody responses to schizont extract. Volunteers will also be screened for significant medical conditions before enrolling in CHMI. Blood-stage malaria infection after 6.5 days of incubation in the liver will be assayed twice daily to monitor the density of infection and anti-malarial treatment will be given either: (a) when the density of infection rises past a threshold of 500 parasites per µl (a threshold substantially lower than 2,500 parasites per µl at which clinical illness becomes more common in children in Kenya
^40^) without signs and symptoms; (b) if a volunteer develops symptoms or signs of illness and an immediate blood film examination shows any evidence of detectable malaria parasites; or (c) the volunteer reaches day 21 of monitoring, at which point CHMI will be completed (
Figure 1). During the duration of CHMI, eligible volunteers will be accommodated at an in-patient setting where the volunteers will stay for the entire duration of the challenge (
Figure 1). All volunteers will be provided with and required to use an ITN for the duration of the study.

**Figure 1. f1:**
[figure not shown]
Schematic of CHMI PfSPZ challenge study profile.

### Recruitment

The target volunteer population will be healthy, adult volunteers. Recruitment will target residents of Ahero in Kisumu County, Western Kenya and residents of Kilifi County, Coastal Kenya by a team of community health workers and fieldworkers respectively. Investigators will emphasize that participation in the study is voluntary. Participant information sheets will be given to interested volunteers. Individuals who feel that the trial is potentially appropriate for them will be invited to attend a formal screening visit with a study clinician. Recruitment in Kilifi will target residents within Kilifi North (Ngerenya) and Kilifi South (Pingilikani and Junju) sub-locations of Kilifi County, where malaria transmission is low to moderate
^41^. Recruitment in Kisumu will target residents of Ahero where transmission is high
^42^.

In Kilifi, community wide meetings to inform potential volunteers about the study will be conducted in the sub-locations followed by meetings with smaller groups of potential volunteers who are interested in participating by fieldworkers. In Ahero, community health workers will conduct meetings with smaller groups of potential volunteers. Volunteers from Ahero will have to be fluent in Kiswahili and/or English, as they will be asked to travel to Kilifi for the challenge event.

Recruitment for the social science component will involve only volunteers who are recruited, consented, and eligible to be enrolled for PfSPZ Challenge administration. Following recruitment to the CHMI study, volunteers will undergo a separate consenting process
^38^ to take part in the social science arm of the study. In addition, relevant stakeholders involved in the study including study clinical and research staff, community representatives and/or field workers will be recruited and consented for participation in this aspect of the study. All volunteers in this part of the study will be recruited after a process of information giving about this component of the study. All consent forms are available to view on Harvard Dataverse
^39^.

### Screening

All potential volunteers will have a screening visit either at the clinical facility in Ahero (Ahero Clinical Trials Unit, ACTU) or in Kilifi at the Kenya Medical Research Institute Wellcome Trust Research Programme (KEMRI-WTRP) which may take place up to 120 days prior to enrolment into a CHMI cohort. The screening visit will involve assessment of malaria past exposure using both laboratory tests and history. Informed consent will be taken before screening. If consent is obtained, the screening procedures indicated in the schedule of procedures (
Table 2) will be undertaken. Abnormal clinical findings from the medical history, clinical assessment or blood tests at any point in the study will be assessed. If a test is deemed clinically significant it may be repeated to confirm the result. If an abnormal finding is deemed to be clinically significant, the volunteer will be informed and referral to an appropriate medical centre arranged with the permission of the volunteer. Decisions to exclude the volunteer from enrolling in the trial or to withdraw a volunteer from the trial will be at the discretion of the Investigator.

**Table 2. T2:** Schedule of Study Procedures.

Timeline (days in relation to challenge)	Screening	C-1	C	C+1 – C+24	C+35
Window (days)	-120 to -3	0	0	0	±5
ICF and ICF evaluation	X				
Medical History	X				
Clinical Assessment	X	X	X	X	X
Urinalysis	X				
Urinary β-hCG	X	X		X	
ECG	X				
Measurement of Height and Weight		X			
Administration of PfSPZ Challenge			X		
Local and Systemic events reviewed		X	X	X	X
Anti-malarial treatment directly observed				X	

C, PfSPZ Challenge; C-1, day before PfSPZ challenge; C+1, day 1 after PfSPZ challenge; β-hCG, β-human chorionic gonadotrophin; ECG, electrocardiogram. Clinical assessment will be based on tests conducted from blood samples collected.

### Selection of volunteers

***Inclusion criteria***

Healthy adults aged 18 to 45 years.Able and willing (in the Investigator’s opinion) to comply with all study requirements.Informed consent.Use of effective method of contraception for the duration of the study (women only). We will ask female volunteers to come with their family planning records to verify. Effective contraception is defined as a contraceptive method with failure rate of less than 1% per year when used consistently and correctly, in accordance with the product label. Examples of these include: combined oral contraceptives; injectable progestogen; implants of etenogestrel or levonorgestrel; intrauterine device or intrauterine system; male partner sterilisation at least 6 months prior to the female subject’s entry into the study, and the relationship is monogamous; male condom combined with a vaginal spermicide (foam, gel, film, cream or suppository); and male condom combined with a female diaphragm, either with or without a vaginal spermicide (foam, gel, film, cream, or suppository).

***Exclusion criteria***

Any of the following constitutes exclusion criterion:

Use of systemic antibiotics with known antimalarial activity within 30 days of administration of PfSPZ challenge (e.g. trimethoprim-sulfamethoxazole, doxycycline, tetracycline, clindamycin, erythromycin, fluoroquinolones and azithromycin).Receipt of an investigational product in the 30 days preceding enrolment, or planned receipt during the study period.Current participation in another clinical trial or recent participation within 12 weeks of enrolment.Prior receipt of an investigational malaria vaccine.Previous receipt of malaria sporozoites (PfSPZ) as part of the malaria challenge study.Any confirmed or suspected immunosuppressive or immunodeficient state, including HIV infection; asplenia; recurrent, severe infections and chronic (more than 14 days) immunosuppressant medication within the past 6 months (inhaled and topical steroids are allowed).Use of immunoglobulins or blood products within 3 months prior to enrolment.Any serious medical condition reported or identified during screening that increases the risk of CHMI.Any clinically significant abnormal finding on biochemistry or haematology blood tests, urinalysis or clinical examination.Women only; pregnancy, or an intention to become pregnant during the duration of the study.Confirmed parasite positive by PCR a day before challenge i.e. at C-1.

Exclusion criterion on day of PfSPZ Challenge administration:

Acute disease, defined as moderate or severe illness with or without fever (temperature >37.5°C).

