^+^for immune responses.

For HIV diagnostic testing, volunteers will have information provided prior to HIV test counselling. HIV sero-status will be established using the standard rapid diagnostic kits in the lab as per the testing algorithm used by the Kenyan Ministry of Health. Those diagnosed as HIV antibody-positive will be referred to an appropriate health centre for further counselling and treatment. To maintain the confidentiality of those volunteers infected with HIV, we will make it clear that during screening one can be excluded due to a range of conditions (not just HIV), as well as abnormal laboratory results.

***Malaria infection prior to PfSPZ Challenge***. In order to prevent pre-existing malaria infection from interfering with the study, eligible volunteers who are found to be PCR-positive for malaria infection at screening will be treated with 7 days of artesunate (this drug was chosen to avoid other drugs with long half-lives that might interfere with subsequent CHMI), and the volunteer will then be screened again by PCR to confirm that they are negative in the week before being included in CHMI. In the case where a time lag of 10 days or more occurs between screening and challenge, all screened volunteers will be treated with the 7-day artesunate observed dose and a repeat PCR screen undertaken at least three days before CHMI (C-3). CHMI will be undertaken during the dry seasons to avoid high rates of malaria re-infection leading to volunteers being ineligible.

***Preparation and administration of PfSPZ Challenge***. For preparation of PfSPZ Challenge, immediately prior to use, PfSPZ Challenge in cryovials will be thawed individually by partial submersion of the vials for 30 seconds in a 37±1°C water bath. Designated, trained study staff will then prepare, dilute and dispense PfSPZ Challenge to clinical staff. Aliquots of the diluents phosphate buffered saline (PBS) and 25% human serum albumin (HSA) will be provided to the clinical sites by Sanaria Inc. PfSPZ Challenge will be administered using a needle and syringe by DVI.

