### Study treatment

***Clinical reviews***. All clinical care and procedures will be undertaken by a qualified nurse and clinician trained in the study procedures. Following administration of PfSPZ challenge volunteers will remain at the in-patient setting until the endpoint treatment completion. Clinically qualified staff will be available at all times, and standard operating procedures (SOPs) will be established for out-of-hours assessment and management of symptoms. Volunteers and staff at the site will have contact numbers of clinically qualified investigators who in turn can consult a senior clinician at any time during CHMI.

The volunteers will be monitored by clinical staff with experience of managing clinical
*P. falciparum* infection. Resuscitation equipment and anti-malarial drugs will be available at all times. The strain of parasite Pf, NF54 used for CHMI is known to be sensitive to chloroquine, artemether-lumefantrine (AL), atovaquone/proguanil and sulphadoxine-pyrimethamine (SP). These treatments are all known to be effective for uncomplicated malaria. A full treatment course will be given to all volunteers reaching the end of CHMI.

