There will be a deliberate analytical framework generated and applied to the data generated. However, this will be largely guided by the outcomes that will be observed and the results for e.g. qPCR. For instance, for parasite growth rates and liver-to-blood inoculums (i.e. the number of parasites exiting the liver and infected red blood cells), these will be calculated by fitting established models to quantitative PCR data. The growth rate will be regressed against the individual immunological measures such as intensity and/or breadth of antibody responses to parasite antigens. Given the co-linearity of responses, a multivariable model is likely to be more informative in testing our hypotheses that: naturally acquired immunity to malaria depends on responses to specific identifiable antigens; and the overall intensity and/or breadth of antibody responses to parasite antigens are associated with immunity. Rather than simply enter all variables in a single multivariable model, we will consider entering variables in clusters and take forward the independent predictors to a final multivariable model. These clusters will be pre-defined and be based on: (a) biological links (for instance grouping all red cell surface antigens separately from merozoite antigens); and (b) on co-linearity (i.e. on clustering groups of antigens with greatest cross-correlations). We will score breadth as the number of antigen responses in the top quartile and mean intensity as the mean of normalized responses for each antigen. These scores will be determined separately for merozoite antigens and for red-cell-surface antigens. We will therefore reduce the dataset to for instance 50 variables, including functional assays, anti-circumsporozoite antibody levels, responses to schizont extract, and scores for mean intensity and breadth which will be added to the final model which will test the hypotheses mentioned above. To test the hypothesis that there are specific thresholds above which immunological responses control parasite growth, we will examine this final model for non-linearity using multiple fractional polynomials and Hill functions to determine if there are discrete thresholds predicting efficacy according to previously used methods.

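### Recent antibiotics with antimalarial activity are an exclusion, recent antimalarial drugs are not, so growth suppressed by residual drug could be counted as control of growth

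*Protocol article*

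**What the plan says.** Under Exclusion criteria, the only item about drugs active against malaria is "Use of systemic antibiotics with known antimalarial activity within 30 days of administration of PfSPZ challenge". Its examples are all antibiotics: "trimethoprim-sulfamethoxazole, doxycycline, tetracycline, clindamycin, erythromycin, fluoroquinolones and azithromycin". The other items (investigational products, malaria vaccines, earlier sporozoite receipt, immunosuppressants, blood products, medical conditions, abnormal findings, pregnancy) do not reach antimalarials taken as treatment or prophylaxis. The last malaria check in the list is "Confirmed parasite positive by PCR a day before challenge i.e. at C-1".

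Two other places bear on this:

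- Study procedures, on infection before challenge, explains the choice of artesunate: "this drug was chosen to avoid other drugs with long half-lives that might interfere with subsequent CHMI". It adds: "In the case where a time lag of 10 days or more occurs between screening and challenge, all screened volunteers will be treated" with observed artesunate, followed by a repeat PCR.
- Study treatment, Clinical reviews, says of the challenge strain: "NF54 used for CHMI is known to be sensitive to chloroquine, artemether-lumefantrine (AL), atovaquone/proguanil and sulphadoxine-pyrimethamine (SP".

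Screening is a visit "which may take place up to 120 days prior to enrolment into a CHMI cohort". Table 2 ticks medical history at screening only. No drug-level assay appears among the laboratory tests under Study procedures or in Table 7.

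On analysis, Statistics says "The growth rate will be regressed against the individual immunological measures", and then plans a final multivariable model that includes the response to schizont extract and the breadth and intensity scores. Neither part names drug exposure as a covariate or as a reason for leaving a volunteer out.

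**The concern.** The protocol guards against long-acting drug that the study itself would give, and against incidental antibiotics. It does not guard against the same long-acting antimalarials obtained elsewhere by adults living in endemic areas before admission.

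In such a volunteer, residual drug can slow or prevent parasite growth. That is the signal the study attributes to immunity. The volunteer may reach day 21 untreated and complete the challenge normally, so the rule that removes early withdrawals from the primary analysis does not apply.

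Two consequences follow for the primary objective, the correlation of antibody level with growth rate. First, growth varies for a reason unrelated to immunity, which dilutes real associations. Second, recruitment deliberately spans low-to-moderate transmission (Kilifi) and high transmission (Ahero). If antimalarial use is commoner where exposure is greater, drug and antibody rise together. The individual correlations then lean towards protection, which is the kind of confounding by exposure that the Introduction says controlled infection avoids.

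**Working it through.** **Text check.** Does any stated safeguard detect residual drug, or exclude for it?

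- Artesunate course: treats parasites; does not remove a drug already taken.
- Repeat PCR and C-1 PCR: detect parasites. Residual drug makes a negative result more likely, so the volunteer passes.
- C-1 review: new conditions or symptoms since screening; drug use is not named.
- In-patient stay: begins around challenge, too late for earlier doses.
- Analysis: no drug covariate or exclusion named.

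None does.

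**Illustration of size.** The article states no figure on this point. From the article: N = 200, 50 variables, model R² 0.30, increment 0.15. Assumed: two areas of 100; carriage p₀ = 5% in one and p₁ = 20% or 30% in the other; growth lower by d = 1 or 2 SD when drug is present; a null antigen whose mean differs by a = 0.5 or 1.0 SD between areas.

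*Dilution.* Outcome variance becomes 1 + p(1−p)d², with p the overall carriage.

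- 5% vs 20%: p = 0.125. With d = 2, 1 + 0.125×0.875×4 = 1.44, and 0.15/1.44 = 0.104. With d = 1, 1 + 0.109 = 1.11, and 0.15/1.11 = 0.135.
- Power at d = 2, single-variable F test (1 and 149 df): R² = 0.30/1.44 = 0.209, f² = 0.104/(1 − 0.209) = 0.132, noncentrality 200×0.132 = 26.4. Power is 99.9% at α = 0.05 and 96% at α = 0.001.
- On the article's undiluted inputs this test gives over 99.9%, not the stated 80%. That is a separate matter.

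*False association, unadjusted test.* The correlation between the null antigen and growth is

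r = −0.25·a·d·(p₁−p₀) / √[(1 + 0.25a²)(1 + p(1−p)d²)],

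and the two-sided 5% test has shift √200·|r|.

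Example (5% vs 20%, d = 2, a = 1): r = −0.25×1×2×0.15 / √(1.25×1.4375) = −0.075/1.340 = −0.056. The shift is 14.14×0.056 = 0.79, and the rejection rate is P(Z < −1.96 + 0.79) + P(Z > 1.96 + 0.79) ≈ 12.4%.

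| Carriage | d | a = 0.5 | a = 1.0 |
|---|---|---|---|
| 5% vs 20% | 1 SD | 5.7% | 7.4% |
| 5% vs 20% | 2 SD | 7.1% | 12.4% |
| 5% vs 30% | 1 SD | 6.9% | 11.5% |
| 5% vs 30% | 2 SD | 10.5% | 24.2% |

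A simulation of 10,000 trials per cell agrees within one percentage point (5.4% to 23.9%). Most rejections beyond the nominal 5% are in the protective direction.

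*With an exposure marker.* The same simulation was run with one added covariate standing for the schizont-extract response (assumed area difference 1.0 or 1.5 SD, within-area correlation 0.6 with the antigen). Rejection is about 5-6% in most settings. It reaches about 8% only at 5% vs 30% carriage with a 2 SD effect.

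**The case against.** The strongest reply is that the planned analysis already absorbs most of the bias. The article calls the multivariable model likely to be more informative, and its final model carries several plausible markers of exposure. The adjusted results above bear this out, and this part of the reply stands. The bias concerns mainly the individual regressions. Adjustment does not remove the added noise, nor any link between drug use and antibody within an area.

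Second, the inputs are assumptions. The article gives no carriage rate and no drug effect, and does not say that more exposed adults take more antimalarials. With a 1 SD effect at 5% vs 20% carriage, the unadjusted rate is only 6-7%. This stands too.

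Third, partial safeguards exist: history and laboratory assessment of past exposure at screening, investigator discretion, the C-1 review, dry-season challenge and required net use. They may lower carriage, and 120 days is a maximum. None is a stated antimalarial exclusion.

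Fourth, this is a condensed article, and the case report forms it cites are not shown. Prior drug use may be recorded there. But the exclusion list reads as complete, down to the allowance for topical steroids, so this carries limited weight.

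A reader might infer that every exposure-related antigen will look protective, or that the study loses its power. The documents support neither: the first depends on unstated drug use and on ignoring the final model, and the dilution leaves power for the planned effect very high.

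**Conclusion.** The gap is real. As written, the eligibility rule admits volunteers whose growth is suppressed by an antimalarial taken outside the study. This does not fit the protocol's stated reason for choosing artesunate or its account of the strain's sensitivity. In an affected volunteer, slow growth would be counted as control of growth.

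The effect on the primary correlations is unquantified. Under the assumptions shown, null rejection in the unadjusted test is about 6-24% instead of 5%, and close to nominal once an exposure marker is in the model. The lower end applies if the drug effect or the difference in carriage is small. If drug use does not follow exposure, only the added noise remains. The point is worth correcting because the remedy is cheap, not because bias has been shown.

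**What to change.** Reconcile the Exclusion criteria with the rationale under Study procedures. Extend the drug-exposure exclusion to antimalarials other than the study's own artesunate, with the look-back period set by the sponsor, and ask about use again at C-1. With 161 of 200 enrolled at the date given in the article, this reaches at most 200 − 161 = 39 volunteers.

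For those already enrolled, pre-specify the handling before growth is linked to antibodies. The article plans to categorise and publish growth outcomes before developing the immune-correlates analysis, which gives a natural point for this. State a primary or sensitivity analysis that leaves out volunteers with recent antimalarial use known from records or, where stored C-1 plasma and approvals allow, with measured residual drug. Report it beside the all-volunteer result.

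The cost is a short amendment, a few screen failures and a slightly smaller analysis set. An assay would be an extra laboratory test and may need further ethics approval or an amendment under Sample use and storage. The 50 ml at C-1 in Table 3 is blood drawn for plasma and PBMCs, so the plasma actually left must be checked first.
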